#### 4.5. Experimental and comparison groups.

The participants in the experimental group will be randomized to a hybrid cardiac rehabilitation program adapted from the "Cardiac Rehabilitation Delivery Model for Low-Resource Settings" proposed by the International Council of Cardiovascular Prevention and Rehabilitation Consensus Statement (23,28). This program will be delivered by an exercise specialist (physiotherapist). Participation of a nurse, nutritionist, and psychologist is expected in the design phase of counseling materials and as consultants. A referral and consultant physician is considered. Content of the voice calls and text messaging will be extracted from a bank of 137 suggesting (32). The core components in this model are:

- 1) Initial comprehensive assessment: includes evaluation about physical activity, diet, tobacco consumption, overweight/obesity, CVD knowledge, depression screening, return to work, and medications. Additionally levels of lipids, blood pressure, and glycaemia will be reviewed.

67

68

69

[figure not shown]

70

71

- 2) Lifestyle risk factor management: one diet and smoking counseling session (as applicable according to initial assessment results) will be provided by the physiotherapist during the second and third session of exercise. If necessary, a referral to mental health department will be made.
- 3) Exercise sessions: exercise testing with a six-minute walk test (6MWT) will be performed at the beginning of the program to develop an individualized prescription. Then, 10 face-to-face exercise sessions (twice a week) of aerobic and resistance training will ensue, supervised by a physiotherapist. Exercise sessions last 10 minutes at the beginning of the program and are progressed to 60 minutes by the end as tolerated. There will be 5-10 patients per professional in each session. One of the principal purposes of these sessions is to develop patient self-management related to the physical activity habit, and educate them how to monitor exercise intensity at home and in daily life using heart rate and the Borg scale or perceived exertion.
- 4) Transition to unsupervised phase: after 5 weeks with face-to-face exercise sessions all patients will be monitored through mobile technology. Delivery methods will include voice calls and text messaging once a week through to twelve weeks from program initiation. The content will promote physical activity, healthy diet, and medication adherence.

The participants in the control group will receive the standard cardiac rehabilitation that is delivered in participating centers. These programs accounts with physicians, nurses, nutritionists and physiotherapists. The programs will be standardized in participating centers in accordance with guidelines, and will be consistent with initial comprehensive assessment and lifestyle risk factor management as is described for experimental group. Differentially, this programs provide medical evaluation, education sessions about diet and smoking, and the exercise sessions are delivered in 10-12-weeks program.

72

#### 4.6. Outcomes, measures and follow-up.

The **primary outcome** is recurrent cardiovascular events during a minimum of 12 month follow-up. This outcome is a composite of cardiovascular mortality (defined as death by stroke, myocardial infarction or heart failure) and hospitalizations due to a cardiovascular cause (non-fatal stroke, non-fatal myocardial infarction, heart failure, and need for revascularization surgery). Death occurrence will be monitored by study personnel through review of a public registry (Servicio de Registro Civil e Identificación of Chile). The death certificate and any associated medical documentation will be copied for consideration by the adjudicating committee. Hospitalization occurrence will be assessed by study personnel through chart review at each participating center and supplemented by phone calls to participants (in case they received care at another center) every two months, using a standardized script. When the participant reports a hospitalization, all associated documents (i.e., tests and exam reports) will be collected from clinical charts in each center. A central adjudication committee will review all materials. This committee will be composed of three clinician-scientists (at least one will be a cardiology specialist) blinded to participant allocation. Members will make the final decision whether the event is definitive, possible, probable, or if it is rejected, and specify the final hospitalization diagnosis with corresponding ICD-10 code.

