#### Inclusion criteria:

- Subjects 18 year old or over.
- Patients with coronary artery disease, including Acute Coronary Syndrome (Unstable Angina, Myocardial infarction with or without ST elevation) or stable coronary vessel disease diagnosed by coronariography or a stress test.
- Patients treated medically (i.e., medication only) or by thrombolysis, angioplasty, or revascularization surgery.
- Patients able to attend the health center almost twice a week over three months.
- Patients who owns a mobile phone.
- Patients that consent to participate in the study through signing an informed consent form.

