#### 4.3. Sample size.

If there is a true difference in favour of the hybrid exercise-based cardiac rehabilitation of 7% in hospitalization rate, then 254 patients are required (127 per group) to be 80% sure that the upper limit of a one-sided 97.5% confidence interval will exclude a difference in favour of the standard exercise-based cardiac rehabilitation group of more than 6%. Considering anticipated loss of follow-up (10%) and the inclusion of an interim analysis that penalizes the power (interim analysis adjustment using Pocock boundary), 314 patients will be recruited (157 per group).

[figure not shown]

This sample size considered the hospitalization and cardiovascular mortality outcomes that was reported in the systematic review by Anderson in 2016 (14), which totaled 18% in the first year of follow-up in those randomized to exercise-based cardiac rehabilitation. The non-inferiority margin was established as is suggested by the Food and Drugs Administration (FDA) (31), which is 50% of the difference between the standard or current therapy (i.e., standard cardiac rehabilitation) and the placebo (or usual care) obtained from a meta-analysis, in this case the same by Anderson (12%).

65

66

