- Adherence to physical activity recommendations: The World Health Organization (WHO) recommends that adults (including those with CVD) 18 years old or over perform 150 minutes of moderate-intensity aerobic activity or 75 minutes of vigorous activity per week, or a combination of both. The activity must be practiced in >10 minutes bouts in order to be considered. The International Physical Activity Questionnaire (IPAQ) will be administered by trained personnel, which has been validated and used in the local setting (37–39). This instrument assesses physical activity of moderate and vigorous intensity in activities related to work, domestic labour, active transportation, and leisure time, and hence can quantify the energy spent in MET-minutes/week for categorization in accordance with the WHO recommendation.
- Adherence to diet recommendations: Participant adherence to the Mediterranean diet will be measured by the MEDAS, an adaptation of a previously validated 9-item index (40). The 14-item screener includes 5 additional items that facilitate rigorous assessment of adherence to the traditional Mediterranean diet in the present population. Each question is scored 0 or 1. This questionnaire was developed for the Prevención con Dieta Mediterránea (PREDIMED) study (41). Also, the food-frequency questionnaire (FFQ) will be administered by trained personnel to assess food patterns and habits, which will enable recall of the necessary information to determinate de MEDAS. FFQ is the most common tool for use in epidemiological studies and the clinical setting. In Chile, it was administered in the 2010-2011 Food Consumption National Questionnaire (42), and in two other epidemiological studies conducted by our group where it has been validated (43,44).
- Health-related quality of life: Trained personnel will apply the widely used EuroQol five-dimensional three-level (EQ-5D-3L) instrument. It has already been validated, and the utility values have been established for the Chilean population (45).
- Exercise related adverse events: adverse events during exercise, such as myocardial ischemia or malignant arrhythmias, will be communicated to the monitor of the study. Serious adverse event, as death in the exercise session, will be reported to corresponding ethic committee and monitor. All events will be registered for the interim and final analysis.

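### The primary composite defines cardiovascular death too narrowly and does not name angioplasty or unstable angina, while the event rate and margin are described without that list

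*Protocol*

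**What the plan says.** The primary goal (Protocol 3.2.1) concerns recurrent cardiovascular events. Section 4.6 makes the outcome a "composite of cardiovascular mortality (defined as death by stroke, myocardial infarction or heart failure) and hospitalizations due to a cardiovascular cause", and a parenthesis lists the admissions: "non-fatal stroke, non-fatal myocardial infarction, heart failure, and need for revascularization surgery". The abstract repeats the admissions list but does not define cardiovascular death.

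The inclusion criteria in 4.2 cover patients treated "by thrombolysis, angioplasty, or revascularization surgery" and coronary disease "including Acute Coronary Syndrome (Unstable Angina, Myocardial infarction with or without ST elevation".

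Among the secondary outcomes in 4.6, the exercise-related item covers "adverse events during exercise, such as myocardial ischemia or malignant arrhythmias" and gives death in an exercise session as an example of a serious adverse event.

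On the planning figures, section 4.3 states: "This sample size considered the hospitalization and cardiovascular mortality outcomes that was reported in the systematic review". It takes from that review an 18% first-year total and a 12% effect, and sets the margin at half the effect. Section 4.3 uses 6 points; the abstract says 5%.

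**The concern.** The objective and the entry criteria are wider than the events that count. Three gaps follow from the wording.

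- **Death.** The definition is closed. A sudden or arrhythmic death that is not attributed to stroke, infarction or heart failure is not a primary event, although the protocol itself foresees malignant arrhythmia and death during exercise.
- **Angioplasty.** The protocol treats angioplasty and revascularization surgery as different treatments, and only surgery is listed.
- **Unstable angina.** It can qualify a patient for the trial, but readmission for it is not listed.

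A non-inferiority margin guards against accepting a worse program. A fixed absolute margin set for one event rate becomes looser in relative terms if the composite actually analysed has a lower rate.

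**Working it through.** **Inputs.** From Protocol 4.3: control rate 18%, planned hybrid rate 18 − 7 = 11%, margin 6 points, one-sided 0.025, power 80%, 127 per group, 10% loss, Pocock adjustment, 157 per group recruited. From the abstract: margin 5%. Assumption: the list captures a fraction f of the events behind the 18%. The documents do not give f, so a range is shown.

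**The plan's own figure.** n per group = (1.960 + 0.842)² × (0.18×0.82 + 0.11×0.89) / (0.06 + 0.07)² = 7.849 × 0.2455 / 0.0169 = 114.02, so 115, below the stated 127. A continuity correction gives 130, within 3% of 127. Rates of 20% and 13%, which are not in the protocol, give exactly 127. The inflation step reproduces with a two-look Pocock factor of 1.1104: 254 × 1.1104 / 0.9 = 313.4, so 314.

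**Relative risk that the margin tolerates.** RR = 1 + margin / (0.18 f).

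| f | Control rate | RR, 6 points | RR, 5 points |
|---|---|---|---|
| 1 | 18% | 1.33 | 1.28 |
| 2/3 | 12% | 1.50 | 1.42 |
| 1/2 | 9% | 1.67 | 1.56 |
| 1/3 | 6% | 2.00 | 1.83 |

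**Chance of accepting a hybrid that is worse by the full margin on all events (24% vs 18%, RR 1.33).** Evaluable patients: 157 × 0.9 = 141 per group. Assume the harm is proportional across event types, so the captured rates are 0.24 f and 0.18 f and the captured difference is d = 0.06 f.

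P = Φ((margin − d)/SE − c), with SE = √{[0.18f(1 − 0.18f) + 0.24f(1 − 0.24f)]/141}.

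The critical value c is 1.96 without an interim penalty, or 2.178 if the two-look Pocock constant applies at the final analysis.

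Example, f = 1/2: SE = √[(0.09×0.91 + 0.12×0.88)/141] = 0.0365; (0.06 − 0.03)/0.0365 = 0.823; Φ(0.823 − 1.96) = 12.8%.

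| f | Rates | 6 points, c = 1.96 | 6 points, c = 2.178 | 5 points, c = 1.96 |
|---|---|---|---|---|
| 1 | 18% vs 24% | 2.5% | 1.5% | 1.5% |
| 2/3 | 12% vs 16% | 7.0% | 4.5% | 4.3% |
| 1/2 | 9% vs 12% | 12.8% | 8.8% | 7.9% |
| 1/3 | 6% vs 8% | 26.0% | 19.5% | 16.6% |

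With all 157 per group, 6 points and c = 1.96, the figures are 2.5, 7.4, 13.7 and 28.4%.

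**Two checks on the assumptions.**

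- If the harm falls only on listed events, the captured difference stays at 6 points. Then (0.06 − 0.06)/SE = 0 and P = 2.5% for every f. The leniency depends on proportional harm as well as on f.
- Under the planned benefit (RR 11/18 = 0.61), 157 per group and 6 points, power is 91, 89, 90 and 93% at 18, 12, 9 and 6%. A lower rate hardly changes the result there. What changes is the risk of accepting a worse program.

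**The case against.** **The admissions list may not be closed.** It is a parenthesis after a general phrase about cardiovascular causes, and surgery may have been meant loosely to include angioplasty. Section 7.2 mentions an operating manual for event adjudication, which is not shown. This stands as a limit on the reading of admissions. It does not settle the matter, because 4.6 has the committee assign a diagnosis and ICD-10 code without saying which ones count. The death definition leaves no such room, although adjudicators may attribute some sudden deaths to infarction.

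**The source of the rate is not shown.** Section 4.3 does not say how the review defined hospitalization. This stands: the planning figures are described without the list, but that does not prove that they come from a wider endpoint.

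**The calculation is simplified.** Non-inferiority must hold in both the intention-to-treat and per-protocol analyses (4.7), which can only lower the chance of passing. Follow-up runs from one to three years, which raises cumulative risk. Both points stand, so the table shows direction and rough size.

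**Harder events are a defensible choice.** Control patients have more supervised contact and only assessors are blinded, so angina admissions may be detected differently by arm, which blinded adjudication cannot undo. This is a fair reason not to replace the primary outcome with every cardiovascular admission. It does not apply to sudden death.

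A reader might infer that the composite misses much of the objective, or that the margin is simply easier to meet. The documents support neither: they give no share for the omitted events, and the second depends on the assumptions above.

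**Conclusion.** The point holds in a limited form and should be fixed. The exclusion of sudden and arrhythmic death follows directly from the definition in 4.6. The omission of angioplasty and unstable angina follows from the list as written, with less certainty that it was meant to be complete. The expected rate and margin in 4.3 are not tied to the composite to which they are applied.

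The consequence for the margin is conditional on a lower event rate and on a proportional effect. At two thirds to one half of events captured, the chance of accepting a program with a true relative risk of 1.33 is about 7% to 13%, against 2.5% at full capture. It is lower with the Pocock constant or with the 5% margin.

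**What to change.** - In 4.6, define cardiovascular death as any adjudicated cardiovascular death, including sudden and arrhythmic death.
- In 4.6 and the abstract, replace revascularization surgery with unplanned coronary revascularization by angioplasty or surgery.
- State whether readmission for unstable angina counts.
- Report the broader composite, with any adjudicated unplanned cardiovascular hospitalization, at least as a sensitivity analysis.
- In 4.3, restate the expected rate and margin for the composite actually used, and reconcile 6% there with 5% in the abstract.

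The cost is wording in the protocol and the adjudication manual, plus a rerun of the sample size. No new data are needed: deaths and reported hospitalizations already go to the blinded committee, which assigns a diagnosis and ICD-10 code. The downside is that angioplasty is more discretionary than infarction or stroke. Blinded adjudication and the restriction to unplanned procedures limit this only in part.

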#### Secondary outcomes are:

- Cardiovascular risk factor control: the routine lipids and glycaemia test results will be extracted from charts. Methods are the standards in each center. Blood pressure will be assessed at each visit during the follow-up by trained personnel measuring blood pressure three times at 30-second intervals using the standard digital sphygmomanometer with the corresponding cuff size (33). Weight will be measured with a standing scale supported on a steady surface with participants wearing only underwear. Height will be measured on the Frankfort plane positioned at a 90° angle against a metric tape mounted on a wall. These will be used to compute body mass index, and hence obesity. Waist circumference will be measured at 1 centimeter above the navel at minimal respiration.
- Exercise capacity: the indicators for exercise capacity will be "aerobic capacity" evaluated through the 6MWT and "muscle strength" evaluated through a grip strength protocol. Both protocols will be administered by trained staff. The 6MWT will be performed using a 30 meter internal flat corridor with 2 cones marking the distance limits. Patients will be instructed to walk (no running or jogging) as much as possible for 6 minutes. Rest pauses will be allowed as many times as necessary, but the subject should resume walking as soon as possible. Total distance covered during the test will be recorded. All the procedures will be conducted in accordance with the ATS Statement (34). The grip strength protocol will be executed using a Jamar dynamometer, according to a standardized method. Patients will be instructed to sit in a chair with armrests with the shoulder adducted, elbow articulation

73

74

75

[figure not shown]

flexed at 90° angle, forearm in neutral position and wrist between 0 and 30° of dorsiflexion. In this position, the subjects will be asked to perform 3 maximal effort trials with each hand; the highest value will be considered (35,36).

- Adherence to physical activity recommendations: The World Health Organization (WHO) recommends that adults (including those with CVD) 18 years old or over perform 150 minutes of moderate-intensity aerobic activity or 75 minutes of vigorous activity per week, or a combination of both. The activity must be practiced in >10 minutes bouts in order to be considered. The International Physical Activity Questionnaire (IPAQ) will be administered by trained personnel, which has been validated and used in the local setting (37–39). This instrument assesses physical activity of moderate and vigorous intensity in activities related to work, domestic labour, active transportation, and leisure time, and hence can quantify the energy spent in MET-minutes/week for categorization in accordance with the WHO recommendation.
- Adherence to diet recommendations: Participant adherence to the Mediterranean diet will be measured by the MEDAS, an adaptation of a previously validated 9-item index (40). The 14-item screener includes 5 additional items that facilitate rigorous assessment of adherence to the traditional Mediterranean diet in the present population. Each question is scored 0 or 1. This questionnaire was developed for the Prevención con Dieta Mediterránea (PREDIMED) study (41). Also, the food-frequency questionnaire (FFQ) will be administered by trained personnel to assess food patterns and habits, which will enable recall of the necessary information to determinate de MEDAS. FFQ is the most common tool for use in epidemiological studies and the clinical setting. In Chile, it was administered in the 2010-2011 Food Consumption National Questionnaire (42), and in two other epidemiological studies conducted by our group where it has been validated (43,44).
- Health-related quality of life: Trained personnel will apply the widely used EuroQol five-dimensional three-level (EQ-5D-3L) instrument. It has already been validated, and the utility values have been established for the Chilean population (45).
- Exercise related adverse events: adverse events during exercise, such as myocardial ischemia or malignant arrhythmias, will be communicated to the monitor of the study. Serious adverse event, as death in the exercise session, will be reported to corresponding ethic committee and monitor. All events will be registered for the interim and final analysis.
- Adherence: attendance at each supervised session, and also adherence to the calls in the intervention group will be collect.

All outcomes will be measured at the beginning of the program, at the end of intervention (10-12 weeks), at 6 months, and at 12 month of follow-up from recruitment in order to capture acute and long-time impact of interventions. Hospitalizations and cardiovascular mortality will be a minimum of one year and a maximum of three year of follow-up in the cases recruited at the beginning of the study. The personnel assessing outcomes will be blinded to intervention assignment.

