### Secondary goals:

- To compare the effectiveness of the abbreviated cardiac rehabilitation programs with the standard program in terms of:
  - o cardiovascular risk factor control (dyslipidemia, hyperglycemia, hypertension, obesity)
  - o exercise capacity
  - o adherence to physical activity recommendations
  - o adherence to diet recommendations
  - o health-related quality of life
  - o exercise related adverse events

**Methodology:** A non-inferiority, pragmatic, multicenter, parallel, single blinded, randomized clinical trial will be conducted. 314 patients with coronary artery disease including Acute Coronary Syndrome (Unstable Angina, Myocardial infarction with or without ST elevation) or stable coronary vessel disease diagnosed by coronariography or stress test, who have received medical treatment, thrombolysis, angioplasty or revascularization surgery will be recruited consecutively, with written informed consent. Participants will be assigned to experimental or standard rehabilitation programs using a permuted blocked randomization scheme. Concealment of assignment will be preserved. The experimental cardiac rehabilitation program includes medical evaluations, 10 face-to-face exercise sessions, diet and smoking counseling, and distance monitoring with text messages and phone calls, delivered by a physiotherapist. The standard cardiac rehabilitation consists of medical evaluation, 20-24 face-to-face exercise sessions, as well as education sessions about diet and smoking, delivered by a nurse, nutritionist and physiotherapist. The main outcome is a composite of cardiovascular mortality and hospitalizations due to cardiovascular causes (non-fatal stroke, non-fatal myocardial infarction, heart failure, and need of revascularization surgery). Secondary outcomes are cardiovascular risk factor control, exercise capacity, adherence to physical activity and diet recommendations, health-related quality of life and exercise-related adverse events. The outcomes will be measured at the end of intervention, at 6 months, and at 12 month follow-up from recruitment. Only main outcome will be a maximum of three year of follow-up. The sample size was calculated considering 5% of non-inferiority limit. Per protocol and intention to treat analysis will be considered. A survival analysis will be run for the primary outcome. One interim analysis is planned when 50% of patients have completed the evaluation at the end of the first year of follow-up.

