#### 4.7. Analysis plan.

The analysis plan will include the following:

1. Baseline data analysis will be conducted in order to compare the distribution of sociodemographic and clinical characteristics of participants to test for homogeneity of groups with randomization.
2. Consider compliance with the rehabilitation study protocol at each center and in both arms,
3. Describe and compare participant adherence to the interventions (including voice calls),
4. Consider loss to follow-up to evaluate presence of bias, and eventually adjust in effectiveness analysis
5. An interim analysis for primary outcome in order to assess whether the trial is unlikely to show non-inferiority at the final analysis will be performed when 50% of the sample has been recruited and followed-up 1 year (46).
6. To test the primary hypothesis, recurrent cardiovascular events, differences in proportions will be estimated in absolute and relative ways as absolute risk difference (ARD) and relative risk (RR), respectively. Additionally, a survival analysis will be performed to estimate hazard ratio (HR).
  - a. Both, intention to treat (ITT) and per protocol (PP) analysis will be considered since the ITT makes easier to established the non-inferiority and the PP is considered a more conservative approach. Non-inferiority will be considered established if both ITT and PP analyses support it (31).
  - b. Analyses will be adjusted if unbalances in baseline characteristics are found
7. Depending on the results, subgroup analysis (e.g., sex) may be conducted to explain unexpected differences in outcomes
8. To test the secondary outcomes: For categorical outcomes both, ARD and RR will be estimated. For continuous outcomes, mean differences will be calculated.

[figure not shown]

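### The protocol sets out no way to find non-hospitalized adverse events in unsupervised exercise, so a safety comparison resting on 10 against 20-24 observed sessions may be biased

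*Protocol*

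**What the plan says.** Protocol section 3.2.2 and the abstract list exercise-related adverse events among the secondary outcomes on which the two programs are compared.

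**Definition and reporting.** Section 4.6 covers adverse events occurring during exercise, with myocardial ischemia and malignant arrhythmia as examples, and routes them to the study monitor. It continues: "Serious adverse event, as death in the exercise session, will be reported to corresponding ethic committee and monitor". It adds that every event is registered for the interim and final analyses. No question, form, interviewer or diary is named for events that happen away from a session.

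**Observed exercise.** In the hybrid arm, section 4.5 gives "10 face-to-face exercise sessions (twice a week) of aerobic and resistance training will ensue, supervised by a physiotherapist", and then "after 5 weeks with face-to-face exercise sessions all patients will be monitored through mobile technology". For the standard arm the abstract states: "The standard cardiac rehabilitation consists of medical evaluation, 20-24 face-to-face exercise sessions". Section 4.5 adds that "the exercise sessions are delivered in 10-12-weeks program".

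**Contacts outside sessions.** For the hybrid arm only: "Delivery methods will include voice calls and text messaging once a week through to twelve weeks from program initiation". Their purpose is given as: "The content will promote physical activity, healthy diet, and medication adherence". In both arms, section 4.6 finds deaths through a public registry, and hospitalizations through chart review and scripted calls every two months. It also schedules measurement of all outcomes at the end of the intervention and at 6 and 12 months.

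**Analysis.** Section 4.7, item 8: "For categorical outcomes both, ARD and RR will be estimated".

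**The concern.** The feature that separates the hybrid from the standard program is that patients exercise with less supervision. The safety question is therefore mainly about what happens when nobody is watching, and that is where the protocol describes no ascertainment for this outcome. An arrhythmia or an episode of ischemia in a supervised session is seen by staff and has a reporting route. The same episode at home, if it does not lead to admission, reaches the trial only if the patient volunteers it.

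The two arms differ about two-fold in the number of sessions staff can observe. If recording follows observation, the hybrid could look safer than it is. An analyst cannot repair this later, because events that nobody asked about cannot be recovered from the database.

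**Working it through.** The protocol gives no event rate or power for this outcome, so there is no planned figure to reproduce. The check asks how far incomplete capture could move the relative risk.

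**Inputs from the protocol**
- Supervised sessions, hybrid: 10 (section 4.5).
- Supervised sessions, standard: T = 20 or 24 (abstract).
- Patients per arm: 157 (section 4.3).

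**Assumptions (not in the protocol)**
- Equal true risk per session in both arms, and rare events.
- Equal total exercise of T sessions, so hybrid patients do T − 10 sessions unsupervised.
- All in-session events are captured; a fraction s of unsupervised events is captured.

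**Step 1. Apparent relative risk, hybrid to standard, when the true value is 1**

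RR = [10 + (T − 10) × s] / T

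| s | T = 20 | T = 24 |
|---|---|---|
| 0 | 10/20 = 0.50 | 10/24 = 0.42 |
| 0.25 | 12.5/20 = 0.63 | 13.5/24 = 0.56 |
| 0.5 | 15/20 = 0.75 | 17/24 = 0.71 |
| 1 | 20/20 = 1.00 | 24/24 = 1.00 |

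**Step 2. Higher risk when exercising alone.** Let unsupervised sessions carry twice the risk (an assumed figure). The true RR is [10 + 2(T − 10)]/T, which is 30/20 = 1.50 or 38/24 = 1.58. At s = 0.5 the recorded RR is [10 + 2 × 0.5 × (T − 10)]/T = T/T = 1.00 for either T. At s = 0 it stays at 0.42-0.50 whatever the home risk.

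**Step 3. Home exercise in the standard arm too.** Let standard patients do H further home sessions at the same total dose. Then

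RR = [10 + (T + H − 10) × s] / (T + H × s)

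At s = 0.5, with H from 12 to 36, this runs from 23/30 = 0.77 (T = 24, H = 12) to 33/38 = 0.87 (T = 20, H = 36). The distortion shrinks.

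**Step 4. Can the direction reverse?** Yes. Suppose the weekly hybrid calls lift home capture to 0.75 in that arm against 0.25 in the standard arm, with T = 20 and H = 24. Then RR = (10 + 34 × 0.75)/(20 + 24 × 0.25) = 35.5/26 = 1.37, against the hybrid.

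**Step 5. Likely counts.** At an assumed 0.001 events per session, expected in-session events are 157 × 10 × 0.001 = 1.6 in the hybrid arm and 157 × 20 × 0.001 = 3.1 to 157 × 24 × 0.001 = 3.8 in the standard arm. At 0.005 they are 7.9 against 15.7-18.8; at 0.0001, 0.16 against 0.31-0.38.

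**The case against.** The case for the protocol has real substance.

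- **The definition is not confined to sessions.** Section 4.6 speaks of events during exercise and registers all of them. The in-session death is an example, not a restriction. This stands: session-only capture is an inference from the absence of any other stated route.
- **All outcomes are scheduled at later assessments.** This stands as a general commitment. But the same sentence includes the start of the program, before any program exercise, and it names no adverse-event question. The content of the two-monthly script is not shown; it is described only for hospitalizations.
- **The gravest events are found anyway.** Deaths come from the registry and cardiovascular hospitalizations from charts and calls, in both arms and in any setting. A reader might infer that home-exercise events are simply missed. For these events that is wrong. What remains open is whether they are attributed to exercise, and what happens to events without admission. Malignant arrhythmia, one of the protocol's own examples, is also not among the hospitalization components listed for the primary outcome.
- **The analysis is legitimate.** A reader might infer that a per-patient risk difference and relative risk are wrong because session numbers differ. They are not. The programs differ in sessions by design, and events per randomized patient is a sound comparison if capture is complete. The choice of further denominators may also sit in an SAP that is not at hand.
- **The outcome is secondary, and counts will probably be small.** This stands. The point does not touch the non-inferiority decision, and with a handful of events any relative risk will be imprecise.

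**Conclusion.** The point holds as a weakness in ascertainment. The protocol describes how in-session events reach the monitor. It describes no way to find non-hospitalized events in unsupervised exercise, or to record whether a death or hospitalization occurred during exercise. With 10 observed sessions against 20-24, the comparison may be biased, probably towards the hybrid.

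Under equal risk and equal total dose, the recorded relative risk would range from 0.42-0.50 with no home capture to 1.0 with full capture. The capture fraction, the amount of home exercise and the event rates are all assumptions.

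A reader might go further and say that the design favours the hybrid by construction. The documents do not support that. It requires zero capture of home events, which the protocol does not state, and the hybrid-only weekly calls could raise reporting in that arm enough to reverse the direction, as step 4 shows. In either direction the comparison would be hard to interpret. The correction is cheap and should be made, since missing data collection cannot be restored at the analysis stage.

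**What to change.** Add the same fixed questions in both arms, covering events during or soon after any exercise, to the existing two-monthly call script and to the end-of-intervention, 6-month and 12-month assessments. Word them so that the answer need not reveal the setting or the arm, to protect the blinding of assessors. Register positive answers by the same route as in-session events, and apply the questions to any death or hospitalization so that its relation to exercise is recorded.

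Keep the per-patient risk difference and relative risk. Show in-session events per attended session in a separate table; section 4.6 already collects attendance at each supervised session, so the denominator needs no new data.

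The cost is a few script questions, one extra table and some recall error in self-reported events. That error should be more alike in the two arms than under the present arrangement, because both are asked the same questions at the same times. The hybrid-only calls remain a difference in contact, so the bias is reduced and not removed.
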